**4. JUDGING CRITERIA**

### 4. PRIMARY OUTCOME

The primary outcome of this study is the variation in mean pain intensity during the previous week, rated on an VAS (from 0 = no pain to 10 = maximum imaginable pain), before and after management between the 2 groups of patients (FR vs SM). Pain intensity on VAS is a validated clinical criterion for the global assessment of the discriminative and emotional aspects of pain *[Price 1994].*

We chose to assess the intensity of the overall pain and not the intensity of the different types of pain. Indeed, we believe that this type of intervention can have a non-specific effect on pain and therefore reduce the perception of pain in general and thus improve the daily life of patients. The variation corresponds to the raw delta between the VAS score at baseline (V1) and that after the 4 sessions of FR vs SM at the last visit (V5).

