## SECONDARY OUTCOMES

The impact of the management in the 2 groups of patients (FR vs SM) will also be evaluated through:

1. The number of responding patients, i.e. who have at least a 30% improvement in their pain on VAS after overall management.
2. The kinetics of the pain intensity curve (assessed with the VAS over the last 7 days) between baseline and each visit. There are therefore 4 mean deltas for each group of patients *[Price 1994].*
3. At the deltas of the following scores, before and after global management:
   - of the KPPS *[Chaudhuri 2015]* which is a reliable and validated scale in the assessment of pain intensity in Parkinson's disease. It includes 14 questions grouped into 7 areas.

Each item is rated according to severity (between 0 and 3) and multiplied by frequency (between 0 and 4). A subscore between 0 and 12 is obtained for each item. The total score is between 0 and

168 by adding up all the sub-scores.

- - of the BPI *[Brasseur 1997]* which evaluates different dimensions of pain such as functional disability, as well as social and psychological impacts. It includes 7 items that patients rate between 0 (no discomfort) and 10 (maximum discomfort).
  - of Mac Gill *[Turk 1985]* which is a self-questionnaire that describes the type of pain and quantifies its intensity. It evaluates the sensory-discriminative dimension and the affective dimension of pain separately. There are 15 items, 8 of which are for the sensory-discriminative dimension and 7 for the affective dimension. Each item is rated between 0 (absent) and 4 (strong).
  - 3PDQ, which is a self-questionnaire currently being validated in France that would make it possible to diagnose primary Parkinson's pain. It includes 20 closed-ended questions.

1. At the threshold of subjective pain perception to heat and tolerance to heat. For each patient in ON condition (i.e. when the patient has taken his or her anti-Parkinson's treatment in the usual way) we will determine their variations:
   - - before/after the session at visit 1,
     - before/after the session at visit 4,
     - between V1 and V4 before the session is carried out,
     - between V1 and V4 after the session has been carried out, - .

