**6. ELIGIBILITY CRITERIA**

## INCLUSION CRITERIA

- Men and women ≥ 18 years old.
- Patients with no disabling dyskinesias judged by the investigator.
- Patients with chronic pain of any origin, regardless of the pathophysiological mechanism, for at least 3 months with VAS ≥ 4.
- Patients whose anti-Parkinson's treatment has been stable throughout the duration of the study and at least for 4 weeks.
- Person affiliated to or beneficiary of a social security scheme.
- Free, informed, written, and signed consent by the participant and the investigator (no later than the day of

, inclusion and prior to any review required by the research).

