**11. STATISTICAL ASPECTS**

### CALCULATION OF THE STUDY SIZE

We will include 30 patients in this study divided into 2 groups of 15 patients. The calculation is based **on the expertise of Centre Expert Parkinson** in Parkinson's disease and more particularly in the associated pain and **on data from the literature**. In assessing pain in

Parkinson's disease by means of VAS, an average reduction of 20 mm on EVA is considered to be

clinically significant (bilateral test), with an alpha risk = 0.05 and a beta risk = 0.20. The standard deviation is 1.5 on an AVE in Parkinson's patients.

With these data and by calculating the number of subjects, 12 patients per group appear to be necessary. With an estimated risk of patients leaving the study at 25%, it is therefore necessary to recruit 15 patients per group.

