**THIS CALCULATION WAS CARRIED OUT BY THE RESEARCH METHODOLOGICAL SUPPORT UNIT.**

### STATISTICAL METHODS USED

Data analysis:

The data processing that will be carried out will be in accordance with the MR-001 reference methodology and therefore meets the CNIL and GDPR expectations, the data in this study will be pseudonymized and protected. A randomization list will be created to randomly determine patient groups.

A detailed flow-chart will describe the flow of subjects in the study. In particular, the number of subjects screened for eligibility, the number of eligible subjects, the number of subjects included and followed up at each visit will be mentioned. The reasons for refusal to participate and to leave the study will be described at each stage.

A descriptive analysis of the entire recruited population will be carried out to verify if there are any deviations from the protocol at the time of inclusion. Quantitative variables will be expressed as ± average standard deviation, range, medians and interquartile ranges, and qualitative variables will be expressed as numbers and percentages.

The analysis is conducted on the intention-to-treat population.

To meet the main objective, we will first describe the VAS score at Baseline (V1) and after all PR sessions (V5) by means of a "box plot" graph. This is in order to better understand the distribution of scores in the 2-stroke and in the 2 groups (as well as 4 box plots). Then we will calculate and describe the variations between V5 and V1. The variation between V1 and V5 is defined by the crude delta between these 2 visits. Finally, we will perform a non-parametric Wilcoxon Mann Whitney test to compare the distribution of variations between the 2 groups of patients.

To meet the secondary outcomes:

1. We will calculate the number of patients with a minimum of 30% improvement on the VAS score between V1 and V5. Thus, if (V5-V1)/V1 is greater than or equal to 30%, the patient is considered to be a responder. We will compare these responder rates between the 2 groups of patients using a Chi2 test.
2. We will perform a non-parametric Wilcoxon Mann Whitney test to compare the distribution of variations at each visit (delta with baseline) between the 2 groups of patients: i.e. 4 tests.
3. For the KPPS and BPI scores and the 3PDQ, we will perform the same analyses as the primary outcome because they are quantitative scores.

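### The 30% responder formula has the wrong sign: applied as written, it counts patients whose pain worsens by 30% or more and excludes every patient who improves

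*Protocol*

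**What the plan says.** The Protocol describes the responder outcome in words and then in a formula.

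- **In words.** Section 4, secondary outcomes, item 1, defines the outcome as "The number of responding patients, i.e. who have at least a 30% improvement in their pain on VAS after overall management". The research summary and the secondary objectives also speak of at least 30% improvement. Section 11, statistical methods used, opens its item 1 the same way: "We will calculate the number of patients with a minimum of 30% improvement on the VAS score between V1 and V5".
- **As a formula.** The next sentence of section 11 makes this operational: "Thus, if (V5-V1)/V1 is greater than or equal to 30%, the patient is considered to be a responder". The responder rates are then compared between the two groups with a Chi2 test.

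Three other statements fix the direction of the scale and the sign of the denominator:

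- Pain is "rated on an VAS (from 0 = no pain to 10 = maximum imaginable pain") (section 4, primary outcome). The same section makes V1 the baseline and V5 the last visit, after the four sessions.
- Benefit is a fall in the score. The sample-size section says that "an average reduction of 20 mm on EVA is considered to be" clinically significant.
- Patients enter with chronic pain "for at least 3 months with VAS ≥ 4" (section 6, inclusion criteria), so V1 is expected to be positive.

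**The concern.** With a positive V1, the ratio (V5-V1)/V1 takes the sign of V5-V1. Less pain at V5 makes it negative, and more pain makes it positive. A threshold of +30% is therefore a threshold for worsening, while the text it is meant to express asks for improvement.

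The formula is the only operational rule that the Protocol gives for this outcome. An analyst who programs it literally would tabulate patients whose pain rose by at least 30% under the label of responders. A treatment that lowers pain would then tend to have fewer of them than sham, the opposite of what the outcome is meant to show.

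**Working it through.** The Protocol states no expected responder rate, power or sample size for this outcome, so there is no figure to reproduce. The check evaluates both rules directly.

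**Inputs from the Protocol.** VAS from 0 to 10, higher meaning more pain; V1 baseline; V5 last visit; V1 of at least 4 at entry.

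- Written rule: (V5-V1)/V1 ≥ 0.30
- Intended rule: (V1-V5)/V1 ≥ 0.30

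| V1 | V5 | Change | (V5-V1)/V1 | Written rule | Intended rule |
|---|---|---|---|---|---|
| 6 | 4.2 | improved | -30% | non-responder | responder |
| 6 | 3 | improved | -50% | non-responder | responder |
| 6 | 0 | complete relief | -100% | non-responder | responder |
| 6 | 6 | none | 0% | non-responder | non-responder |
| 6 | 7.8 | worse | +30% | responder | non-responder |
| 6 | 8 | worse | +33% | responder | non-responder |
| 4 | 5.2 | worse | +30% | responder | non-responder |
| 8 | 10 | worse | +25% | non-responder | non-responder |

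Two results follow without any assumption about the data:

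1. No patient who improves can be a responder under the written rule, because the ratio is negative for all of them.
2. V5 cannot exceed 10, so the written rule requires 1.3 × V1 ≤ 10, that is V1 ≤ 10/1.3 = 7.69. A patient with a higher baseline can never be a responder, whatever happens.

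The ratio has no unit, so recording the VAS in mm out of 100, as the annex form does, changes neither result.

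**Illustration of size, on assumed inputs.** The Protocol gives no baseline mean. It gives a standard deviation of 1.5 on the VAS without saying that this is the SD of the change. Assume a baseline of N(6, 1.5), a change with SD 1.5, and V5 held within 0 to 10. Two ways of imposing the entry floor of 4 were simulated with 400,000 patients.

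| Handling of the baseline | Mean change | Written rule | Intended rule |
|---|---|---|---|
| Clipped to 4–10 | -2 | 0.7% | 54.6% |
| Clipped to 4–10 | -1 | 3.4% | 30.0% |
| Truncated to 4–10 | -2 | 0.6% | 53.2% |
| Truncated to 4–10 | 0 | 10.6% | 11.2% |

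Take the last two rows as the reflexology arm (mean improvement of 2) and the sham arm (no mean change). The intended rule gives 53.2% against 11.2%, a difference of 42 percentage points in favour of reflexology. The written rule gives 0.6% against 10.6%, a difference of 10 points the other way.

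With 15 patients per group, the written rule yields about 15 × 0.006 = 0.1 expected responders under reflexology and 15 × 0.106 = 1.6 under sham. The chance of none in either arm is 0.994^15 × 0.894^15 = 0.17. A significant result in the wrong direction (two-sided 0.05) would occur in about 1.5% of trials with Fisher's test and about 6% with the uncorrected Chi2 test.

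**The case against.** The best defence is that the intent is plain. Every worded definition says improvement, and the formula is introduced as a consequence of the sentence before it, so a careful programmer would notice the mismatch. The error touches one secondary outcome in a study that calls itself exploratory and a pilot, and the Protocol ranks no secondary outcome above another, so first place in the list carries no special weight. A literal analysis would also be less harmful than a mirror-image result. It would most likely give a nearly empty, visibly odd table, and seldom a significant finding in the wrong direction.

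All of that stands as a limit on the reach of the error, and none of it makes the formula right. Nothing elsewhere supplies a sign convention that would rescue it: the variation is described only as a raw or crude delta between V1 and V5. Reading the ratio as an absolute value would not help, since patients who worsen by 30% would still count. Nor would a dropped minus sign before the 30%: a threshold of ≥ -30% would admit nearly everyone without a large improvement. A separate analysis plan does not settle the matter either. If it copies the rule it inherits the error, and if it departs from the rule without comment it changes a prespecified outcome definition without a record.

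**Conclusion.** The point holds. The responder formula in section 11 contradicts the worded outcome in the same item and in section 4, and gives the wrong classification if followed. This rests only on the scale anchors, the visit definitions and a positive baseline, all stated in the Protocol.

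The size depends on assumed inputs. For a mean improvement of 2 points, the written rule would report under 1% responders where the intended rule reports about 53% to 55%; for 1 point, about 3% against 30%. If sham has no mean change and reflexology a 2-point improvement, the apparent direction reverses. With 15 patients per group, that reversal would seldom reach significance.

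Only secondary outcome 1 is affected. The primary comparison of raw changes by the Wilcoxon Mann-Whitney test and the sample-size calculation do not use this formula.

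**What to change.** In section 11, statistical methods used, item 1, replace the condition with: responder if (V1-V5)/V1 ≥ 30%, equivalently (V5-V1)/V1 ≤ -30%. Under this rule 6 to 4.2 is a responder (+30%), 6 to 0 is a responder (+100%) and 6 to 7.8 is not (-30%), in line with the worded definition.

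The cost is one line of wording, carried into the analysis plan and the program. No new data are needed and no other analysis changes. It should be made and recorded before the analysis is programmed, so that it stands as a correction to the prespecified rule.

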**The following questions are only about your most bothersome pain.**

- **In general, does the pain have one or more of the following characteristics:**

|  | **YES** | **NO** |
| --- | --- | --- |
| **Burn** |  |  |
| **Vice** |  |  |
| **Compression** |  |  |
| **Electric shocks** |  |  |
| **Slenderness** |  |  |
| **Painful cold** |  |  |
| **Cramp** |  |  |
| **Dull ache** |  |  |
| **Stabbing** |  |  |
| **Sting** |  |  |
| **Grinding** |  |  |
| **Deep** |  |  |
| **Nagging** |  |  |

- **In general, is the pain associated in the same area with one or more of the following symptoms:**

|  | **YES** | **NO** |
| --- | --- | --- |
| **Tingling** |  |  |
| **Tingling** |  |  |
| **Itching** |  |  |
| **Numbness** |  |  |

- **In general, is the pain caused or increased by:**

|  | **YES** | **NO** |
| --- | --- | --- |
| **Rubbing on the painful area** |  |  |
| **Pressure on the painful area** |  |  |
| **Contact with a cold object on the painful area** |  |  |
| **Contact with a hot object on the painful area** |  |  |

- **Does your pain meet one or more of the following criteria:**

|  | **YES** | **NO** |
| --- | --- | --- |
| **It was one of the first symptoms of Parkinson's disease** |  |  |
| **It is on the side most affected by Parkinson's disease** |  |  |
| **She Increases when your state Engine worsens** |  |  |
| **It is improved by taking antiparkinsonian drugs** |  |  |
| **It is present at night** |  |  |
| **It is present diffusely on your body** |  |  |
| **It moves from one place to another in your body** |  |  |

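### The 3PDQ, a yes/no diagnostic questionnaire with no score defined in the protocol, is analysed as a quantitative measure of pain change

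*Protocol*

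**What the plan says.** Protocol section 11 (Statistical methods used) sets the analysis for secondary outcome 3: "For the KPPS and BPI scores and the 3PDQ, we will perform the same analyses as the primary outcome because they are quantitative scores". The primary analysis it borrows is a change score, "The variation between V1 and V5 is defined by the crude delta between these 2 visits", compared between arms by the Wilcoxon Mann-Whitney test.

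Section 4 (Secondary outcomes) puts the 3PDQ in a list introduced by "At the deltas of the following scores, before and after global management". Section 3 (Secondary objectives) gives its purpose, together with the KPPS and the BPI, as comparing the variation in chronic pain between the two groups. The monitoring table in section 9 schedules it at V1 and V5.

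The instrument itself is described in section 4 as "3PDQ, which is a self-questionnaire currently being validated in France that would make it possible to diagnose primary Parkinson's pain", and then "It includes 20 closed-ended questions". The annex prints it as YES/NO boxes under the instruction "The following questions are only about your most bothersome pain".

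**The concern.** The reason given for the test is that the 3PDQ is a quantitative score. Nothing in the protocol supports that, and the description and annex point to a diagnostic checklist. An instrument meant to say what kind of pain a patient has is being used to say how much the pain changed.

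Section 2 (Justification of methodological choices) says the several questionnaires will be cross-referenced to strengthen what is observed about reflexology. A 3PDQ p-value would then stand beside the VAS, KPPS and BPI results as if it bore on the same question. It does not: the delta can stay at zero although pain has fallen, and it can move because the patient is now describing a different pain.

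**Working it through.** No sample-size or power formula bears on this point. The check is a count of the annex form and a comparison of the relevant sections.

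**1. Item count.** The only figure the protocol gives for the 3PDQ is 20 questions (section 4). The YES/NO rows in the annex are:
- characteristics of the pain: 13
- associated symptoms in the same area: 4
- triggers or aggravating contacts: 4
- further criteria (history, side, motor state, drugs, night, spread): 7

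Total: 13 + 4 + 4 + 7 = 28. The stated 20 is not reproduced.

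**2. Can the delta be formed?** The annex has no total, range, cut-off or direction for the 3PDQ. By contrast:
- the BPI annex sums items A to G;
- the McGill annex gives two subscores and a total out of 60;
- the KPPS annex has domain totals and an overall total;
- the HAD annex gives two totals out of 21.

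Without a rule, several variables are possible:
- a count of yes answers on the annex form: 0 to 28, so a delta from -28 to +28;
- a count on the stated 20 questions: 0 to 20, so a delta from -20 to +20;
- a diagnosis coded 0/1: a delta of -1, 0 or +1.

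The protocol does not say which is meant, or whether a higher value is better or worse.

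**3. Would a count of yes answers measure pain change?**
- None of the 28 rows rates intensity. A patient who meets the protocol's 30% VAS improvement while the pain keeps its character ticks the same boxes, and the delta is 0.
- At least one row is fixed history for a given pain: "It was one of the first symptoms of Parkinson's disease". Another asks whether the pain lies on the side more affected by the disease, which describes type and not severity.
- The first three blocks ask about the pain in general. The VAS covers the last 7 days.

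**4. Is it the same pain at both visits?** The form is limited to the most bothersome pain and asks for its location. No instruction tells the patient at V5 to describe the pain named at V1. Section 2 (Current state of knowledge) says patients may have several types of pain at once. If the pain named at V1 eases, another may become the most bothersome, and the two forms then describe different pains. Section 4 (Primary outcome) deliberately targets overall pain, which is a different quantity.

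**5. Consistency with the protocol's own methods.** Section 1 assigns Chi2 or Fisher to qualitative variables. Section 11 treats yes/no analgesic use as qualitative. The yes/no 3PDQ answers are handled otherwise, and the only reason given is that they form a quantitative score.

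**The case against.** The strongest reply is that scoring rules are commonly left to the statistical analysis plan or the instrument's validation source, neither of which is at hand. A count of yes answers is a legitimate discrete variable, and a Mann-Whitney test on its change is a valid rank test, ties aside; the HAD and KPPS are also sums of categorical items. A fixed history item adds zero to the delta for the same pain, so it adds no error. Intensity is already covered by the VAS and KPPS, and no decision rests on the 3PDQ.

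Much of this stands, and it rules out some stronger readings that a reader might infer:
- *That the 3PDQ has no score at all.* The documents show only that this protocol states none. A rule may exist elsewhere.
- *That it captures whichever pain is worst on the day of the visit.* The feature blocks ask about the pain in general. What is supported is that the V5 pain is not tied to the V1 pain.
- *That a change of index pain would produce a false positive.* Patients are randomised and blinded, so with no difference in effect between arms, switching favours neither. The cost is mainly in interpretation and sensitivity.
- *That the data should simply be reclassified and compared by Fisher's test.* That needs a cut-off, which the protocol also lacks.

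The reply does not rescue the analysis as written. The protocol does more than omit a detail: it asserts the type of variable, names the test and ties the result to variation in chronic pain. A valid rank test on a count of pain features still answers a different question from the one the objective asks.

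**Conclusion.** The point holds, as a minor one. As written, the rule either cannot be applied from the protocol or, if a count of yes answers is assumed, gives a comparison of pain features that does not measure change in pain. The item count is inconsistent, 20 against 28.

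The reach is one secondary outcome in an exploratory trial of 30 patients. The primary VAS analysis, the sample size and the other questionnaires are not affected.

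The conclusion rests on the annex being the form that patients complete, and on no instruction outside the protocol fixing the index pain at V5. A scoring rule found elsewhere would make the delta computable. Unless it contained something other than these yes/no features, it would not turn the result into a measure of intensity.

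**What to change.** 1. In section 11, remove the 3PDQ from the outcomes analysed as a quantitative delta by Mann-Whitney. Remove it from the pain-variation objective in section 3 and from the list of score deltas in section 4, with the matching entries in the section 1 summary.
2. Report the V1 responses, and the V5 responses if that visit is kept, descriptively by arm as pain-type characteristics.
3. Make a between-arm comparison only if the protocol states the scoring or classification rule and the V5 form refers to the pain named at V1. If the result is a classification, use the protocol's own method for qualitative variables (Chi2, or Fisher with small expected counts).
4. Reconcile the number of items between section 4 and the annex.

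Steps 1, 2 and 4 are changes of wording. They need no new data and drop one secondary p-value. Step 3 costs more: it needs a rule that the protocol does not contain, and it changes how the form is given at V5, since the printed instruction lets the patient choose the most bothersome pain.
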